### Sample size

The significance level is set at 0.05, corresponding to a Z-value of 1.96. The power of the test is 90%, corresponding to a Z-value of 1.28. The assumed mean 6MWD values (339 m for the MIRP group and 320 m for the control group) and standard deviations for both variables are given as 20 m, and the resulting effect size used for the sample size calculation was derived from our center’s preliminary pre-study data. These estimates were based on an initial analysis of a small cohort of patients who underwent the intervention protocol prior to the initiation of this formal randomized controlled trial. Finally, there is a non-inferiority margin, denoted as *Δ* = 30, which requires 35 patients per group. A 5% dropout rate has also been accounted for, resulting in the target of 50 participants per group (100 in total).

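### The stated inputs do not give 35 per group, 5% dropout does not take 35 to 50, and 90% is not the power of the design under any reading

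*Protocol article*

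**What the plan says.** The Sample size section of the protocol article sets out the whole calculation in one paragraph:

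- Error rates: "The significance level is set at 0.05, corresponding to a Z-value of 1.96" and "The power of the test is 90%, corresponding to a Z-value of 1.28".
- Assumed mean 6-minute walk distances: "339 m for the MIRP group and 320 m for the control group".
- Spread: "standard deviations for both variables are given as 20 m".
- Source of the assumptions: "These estimates were based on an initial analysis of a small cohort of patients" treated at the centre before the trial.
- A non-inferiority margin of 30, with no unit given, "which requires 35 patients per group".
- Final step: "A 5% dropout rate has also been accounted for, resulting in the target of 50 participants per group (100 in total".

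The Randomization and allocation concealment section gives 1:1 allocation. The Background of the Abstract describes the aim as comparing the effectiveness of the two programmes. A non-inferiority aim appears nowhere outside the Sample size section.

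**The concern.** The paragraph prints every input, the intermediate result, the dropout rate and the final target, so it can be checked line by line. Two links look broken: inputs to 35, and 35 to 50. If both are broken, the 90% does not describe the trial being run. A reader then cannot tell whether 50 per group is generous or short for the question asked, or which question the size was meant to answer, because an assumed 19 m benefit suggests superiority while the margin suggests non-inferiority. That bears on how a result without a clear difference in the primary outcome would be read.

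**Working it through.** **Inputs.** All come from the Sample size section except the 1:1 allocation: z = 1.96 and 1.28, sum 3.24, square 10.4976; SD 20 m, variance 400; difference 339 − 320 = 19 m in favour of MIRP; margin 30, taken as metres.

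**Reproducing the 35.** For two equal groups, n per group = 2 × (z sum)² × SD² / d², where d is the distance between the assumed truth and the null value.

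| Reading | d (m) | n per group |
|---|---|---|
| Superiority on 19 m | 19 | 2 × 10.4976 × 400 / 361 = 23.3, so 24 |
| Non-inferiority, MIRP 19 m better | 30 + 19 = 49 | 2 × 10.4976 × 400 / 2401 = 3.5, so 4 |
| Non-inferiority, no true difference | 30 | 2 × 10.4976 × 400 / 900 = 9.3, so 10 |
| Non-inferiority, 19 m subtracted from the margin | 30 − 19 = 11 | 2 × 10.4976 × 400 / 121 = 69.4, so 70 |

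None gives 35. Using one-sided 0.05 instead gives 19, 3, 8 and 57, so sidedness does not explain it.

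By the exact t-test (noncentral t), superiority needs 25: 24 per group gives 89.6% power and 25 gives 90.8%.

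The only route found to 35 is

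(3.24 × 20 / 11)² = 34.7, so 35.

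This has two faults. It omits the factor 2 for comparing two means. It also uses 30 − 19, although a treatment assumed to be 19 m better lies further from the non-inferiority limit, not nearer to it. Restoring only the factor 2 gives 70.

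**From 35 to 50.** 35 / 0.95 = 36.8, so 37 per group. Multiplying instead, 35 × 1.05 = 36.75, also 37. For 50 to follow from 35, the loss would have to be 1 − 35/50 = 30%. Starting points of 25 and 70 give 25 / 0.95 = 26.3, so 27, and 70 / 0.95 = 73.7, so 74. Neither leads to 50.

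**Power of the actual target.** With 5% loss, 50 × 0.95 = 47.5, so 47 evaluable per group. At SD 20 m and two-sided 0.05 (one-sided 0.025 for non-inferiority), by noncentral t:

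| Distance | 35 per group | 47 per group | 50 per group |
|---|---|---|---|
| 19 m (superiority) | 97.5% | 99.5% | 99.7% |
| 49 m or 30 m (non-inferiority, MIRP better or equal) | >99.9% | >99.9% | >99.9% |
| 11 m (the distance behind the 35) | 62% | 75% | 78% |

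No entry is near 90%.

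**SD limit for superiority.** With 47 per group and a 19 m difference, power is 90.2% at SD 28 m and 89.4% at SD 28.4 m, so 90% is kept up to about 28 m.

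**The case against.** The arithmetic cannot be rescued from elsewhere: no other section explains the 50, and neither condensed reporting nor a separate analysis plan can reconcile figures printed side by side. Four cautions do stand.

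- **Direction.** A reader might infer that the trial is too small, or simply that its power is 99.5%. The documents support neither. On superiority, or on non-inferiority with MIRP better or equal, 50 per group is more than enough at the stated inputs. Only the 11 m distance makes it short. On the superiority reading, a null result at these inputs would be more informative than 90% power suggests.
- **Choice of hypothesis.** Rewriting the paragraph as superiority removes the margin. That is a design decision for the sponsor, not a typographical repair.
- **The SD.** It is tempting to say that 20 m is too small. It implies that about 95% of controls walk between 281 and 359 m (320 ± 1.96 × 20), and it came from a small cohort. But the article discloses that source and gives no other SD, so nothing in it shows 20 m to be wrong. For assumed SDs of 30 and 40 m, which are not in the document, superiority power with 47 per group would be about 86% and 62%. On non-inferiority with MIRP 19 m better, power would still be over 99.9% at 40 m. This is a sensitivity remark, not part of the error.
- **Timing.** The Trial status section has recruitment ongoing in August 2025 and database lock planned for December 2025. Correcting the text will not change the data. It changes only whether the stated justification is true.

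**Conclusion.** Wrong as written. The 35 per group does not follow from the stated inputs by any valid two-group formula tried; the valid answers are 25 (24 by normal approximation) for superiority and 4, 10 or 70 for non-inferiority. A 5% allowance gives 37, not 50, and this second contradiction holds whatever the hypothesis. The 90% is not the power of 50 per group: it is about 99.5%, over 99.9% or about 75%, according to the reading. The conclusion rests on the article's own means, SD and z-values, on a margin in metres, and on 47 evaluable per group. It does not establish that the trial is underpowered or that the SD is mistaken. That the 35 came from the 11 m formula is an inference from the matching number, since the article shows no formula.

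**What to change.** Correct the Sample size section and leave enrolment as it is.

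1. State whether the primary comparison tests superiority or non-inferiority. The aim in the Abstract and the assumed 19 m benefit fit superiority. If that is the sponsor's decision, remove the margin explicitly and say so. If non-inferiority is kept, give the margin's unit, the assumed true difference with its sign, and the two-group formula.
2. Give figures that match. For superiority, the text could read: *A two-sided t-test at 0.05 for a difference of 19 m with SD 20 m needs 25 per group for 90% power (27 with 5% loss). We randomise 50 per group; with 47 evaluable this gives about 99.5% power, and at least 90% power up to an SD of about 28 m.*
3. State the dropout rate, or the other reason, that actually led to 50.

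A sentence on larger SDs is optional and should label them as assumptions. The cost is a text correction: no extra patients and no new data. The drawback is a less tidy justification, since the article would have to acknowledge that 50 was not reached by the route now printed.

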### Recruitment

Patients who have just returned to the regular ward from the intensive care unit are screened for eligibility within the first 24 h, and informed consent is obtained from each participant by trained research staff. For patients who do not initially meet eligibility criteria during this first 24 h screening, the reasons for exclusion will be recorded. These patients will be re-assessed every 24 h. If they meet the eligibility criteria within 3 days, they will be enrolled in the study. If they meet the criteria after 3 days, they will not be enrolled or included in the study analysis; however, they will continue to receive standard rehabilitation care and undergo regular clinical assessments. Strategies to raise trial awareness have been implemented. Patients are informed about the postoperative rehabilitation program during preoperative discussions, provided with a brief rehabilitation information sheet, and exposed to educational posters permanently displayed in the ward. A small group of lung transplant recipients and their caregivers reviewed the patient information posters and the short information sheet. Their feedback was incorporated to ensure the materials were clear, understandable, and relevant to the target patient population.

### Common rehabilitation methods for both groups

Positioning was used to promote respiratory mechanics while ensuring patient safety. Caregivers performed all positioning interventions in bed, including guided adjustments of the patient’s hips, scapula, and trunk to optimize lung expansion. Sitting out of bed or transferring to a bedside chair was performed under the supervision of a physiotherapist until the therapist confirmed it was safe and authorized the caregiver to perform it independently. Patients maintained an upright position in bed for 15–30 min, at least four times daily, with gradual extension up to 2 h as tolerated. Blood pressure and symptoms were monitored to ensure safety during the intervention. To encourage early mobilization, patients were educated to reduce prolonged bed rest; for instance, if a patient had been resting in bed for 2 h, they were encouraged to attempt sitting upright. Position changes were also performed to reduce skin pressure until patients could maintain the upright position independently (Figure 2).Activities of daily life guidance involve patients turning over and getting up, sitting balance, sitting center of gravity transfer, bed-to-wheelchair transfer, from sitting to standing, walking, and other movements for guidance and training.

**Figure 2 fig2:**
[figure not shown]
Positioning of a patient during sitting training. The upper left arrow points to a supportive pillow behind the patient’s back, facilitating an upright trunk position. The upper right arrow shows the support under the elbow against the bed rail, which helps stabilize the torso. The overall arrangement allows for the simultaneous use of nasal oxygen/enteral tubes, intravenous access, and monitoring leads without interference.

The supervised intervention concludes at 6 weeks for all participants, at which point they are provided with a standardized, personalized plan for unsupervised rehabilitation. This plan is continued until the 3-month assessment, regardless of whether the patient has been discharged or remains in the hospital.

### Intervention arm (MIRP)

Chest Physical Therapy Combined with Airway Clearance Techniques. In the intervention arm, chest physical therapy (CPT) is combined with airway clearance techniques (ACTs) as an integrated intervention. During each session, trained physiotherapists place their hands in a semicircle on the lower edge of the patient’s ribs to provide manual assistance. Guided by these hands-on techniques, patients perform deep inhalation with a 2–4 s breath hold as part of thoracic expansion techniques (TETs). During exhalation, a low-pressure oscillatory positive expiratory pressure (OPEP) device (10 cmH₂O, 12–14 Hz) is used, while the physiotherapist provides rib cage compression (RECC) and manual chest wall vibration to facilitate mucus clearance. Each set is repeated 3–5 times, with a 1 min rest between sets, and 5–8 sets are performed per session, five times per week.Inspiratory Muscle Training Transcutaneous Diaphragmatic Nerve Stimulation. IMT is performed using a threshold device, with an initial load set at 50% of the patient’s maximal inspiratory pressure (MIP). Each session consists of 30 repetitions conducted five times per week. The training intensity is progressively adjusted according to patient tolerance and improvement in respiratory strength. Transcutaneous diaphragmatic nerve stimulation is applied using surface electrodes. The active electrode is positioned at the lateral edge of the sternocleidomastoid muscle, at the lower third, while the reference electrode is placed at the second intercostal space along the mid-clavicular line. Stimulation parameters are set at 40 Hz, with current intensity adjusted to a tolerable range of 10–30 mA. Each session is conducted under the supervision of a physiotherapist to ensure safety and optimize diaphragmatic activation.Aerobic training combined with Neuromuscular Electrical Stimulation. Recumbent cycling is for bedridden patients, starting at 10 min and gradually increasing to 20 min. Patients are encouraged to actively participate, targeting an intensity of 4–5 on the Borg Fatigue Scale, three times a week. Patients who can leave the bed and transfer to a wheelchair should switch to seated cycling, with continuous exercise for 20 min per session, at an intensity of 4–5 on the Borg Fatigue Scale, five times a week. The NMES is incorporated into the recumbent cycling training, using modulated medium-frequency electrical stimulation, which is delivered through 4 × 4 cm self-adhesive gel electrodes. A bipolar electric current was applied with a frequency of 75 Hz and a pulse duration of 50 μs (5 s on and 5 s off).Lower extremity resistance training: It uses freehand resistance methods, targeting the knee extensors, hip extensor muscle group, and hip abductor external rotator muscle group. Each exercise is performed for 1–3 sets, with 8–12 repetitions per set, twice a week. The principle of freehand resistance is to use the maximum resistance that allows the full range of joint movement, twice a week.Intensive swallowing therapy: It consisted of pharyngeal electrical stimulation (PES) combined with traditional swallowing exercises, both administered by a certified speech-language pathologist (SLP). The swallowing exercise regimen, tailored based on the individual’s Kubota drinking test or volume-viscosity swallow test (VVST) results, included sensory and motor techniques such as thermal-tactile stimulation, effortful swallow, and the Mendelsohn maneuver. This combined therapy (PES + exercises) was conducted for 30 min per session, three times per week.Nutrition Specialist–Managed Nutrition: Patients are managed directly by a nutrition specialist. The specialist closely monitors actual nutritional intake, including calories, protein, and fluid balance, and evaluates laboratory indicators (e.g., albumin, prealbumin, and electrolytes) to assess nutritional status. Based on these assessments, the nutrition plan is dynamically adjusted to meet individual patient needs, including modifying nutrient composition, supplementation, or feeding routes. The nutrition specialist also provides ongoing guidance to the clinical team to ensure adherence to the plan, thereby optimizing postoperative nutritional support.

### Control arm (standard care)

Chest physical therapy techniques are administered by physical therapists. The therapist places their hands in a semicircle on the lower edge of the patient’s ribs, first following the patient’s breathing frequency and amplitude. Upon the patient’s long exhalation command, the therapist gently applies downward and inward pressure on the patient’s thorax as they exhale. Then, the therapist releases the pressure and instructs the patient to inhale deeply, using their fingers to slightly lift the thorax upward and outward to promote deep inhalation. This procedure is repeated 3–5 times per set, with a 1 min break between sets, and 5–8 sets are performed per session, five times a week.Inspiratory Muscle Training is performed using a threshold device, with an initial load set at 50% of the patient’s maximal inspiratory pressure (MIP). Each session consists of 30 repetitions, conducted five times per week. The training intensity is progressively adjusted according to patient tolerance and improvement in respiratory strength.Aerobic training includes two types of bicycle training: horizontal and seated. For bedridden patients, horizontal cycling starts at 10 min and increases to 20 min as tolerated, with an intensity of 4–5 on the Borg Fatigue Scale, performed three times a week. Patients who are able to transfer from bed to wheelchair switch to seated cycling for 20 min per session at the same intensity, also three times a week.Lower extremity resistance training involves using freehand resistance to target knee extensors, hip extensors, and hip abductor external rotators, with each exercise performed for 1–3 sets of 8–12 repetitions, once a week. The resistance should be the maximum that allows the full range of motion.Swallowing therapy comprises traditional swallowing exercises administered by a certified speech-language pathologist (SLP). The exercise regimen was similarly personalized based on findings from the Kubota drinking test, or VVST, focusing on techniques such as thermal-tactile stimulation, effortful swallow, and Shaker exercises. This standard therapy was conducted for 30 min per session, twice per week.Pulmonologist–managed Nutrition (PN): After receiving training from a lung transplant–specialized nutritionist, the pulmonologist develops a nutrition plan for each patient. The plan mainly includes the route of nutritional support, target nutritional intake, and basic monitoring indicators.

### Outcome measurement

The selection of assessment time points was based on clinical relevance and the study objectives. The 6-week assessment was chosen to evaluate the short-term efficacy and immediate impact of MIRP upon completion of the supervised, intensive intervention phase. The 3-month assessment serves as a key mid-term follow-up point to determine the sustainability of initial gains and to capture clinically significant outcomes as patients transition into the maintenance phase of recovery. All outcome assessments will be conducted by trained research assistants who are blinded to the participants’ group allocation. The primary outcome measure of treatment failure is assessed at 3 months after recruitment. The following are assessed at 6 weeks and 3 months after recruitment, including:

Short-term change in health-related quality of life, based on the modified Barthel Index and 36-Item Short Form Health Survey (SF-36).Body skeletal muscle mass and bone mineral density were assessed using dual-energy X-ray absorptiometry; limb muscle strength was evaluated by measuring isometric knee extension strength using a handheld dynamometer (expressed in kg); limb dimensions were determined by measuring the circumference of the thigh and calf using a non-elastic tape measure; global muscle function was scored using the Medical Research Council (MRC) Scale for muscle strength, which provides a composite score (ranging from 0 to 60) based on the manual testing of six key muscles bilaterally.Respiratory muscle and lung function were comprehensively evaluated using the following objective measures: maximum inspiratory pressure (MIP) to assess inspiratory muscle strength, standard spirometry for lung function parameters, and diaphragmatic ultrasound to quantify diaphragmatic excursion and thickening fraction (TFdi) as key indicators of diaphragmatic performance. Patient-reported dyspnea was assessed using the St. George’s Respiratory Questionnaire (or Dyspnea Rating Scale).Psycho-emotional states, based on the Anxiety Self-Rating Scale and Depression Self-Rating Scale.The state of swallowing function and nutrition, based on the Toronto Dysphagia Bedside Screening Test, 10-item Eating Assessment Tool (EAT-10) Swallowing Screening Scale, grade, roughness, breathiness, asthenia, and strain (GRBAS) grading scale for hoarseness of voice, and the Mann Assessment of Swallowing Ability Scale (MASA).Adverse Events Monitoring: All adverse events (AEs) occurring during or within 24 h of a rehabilitation session were recorded. Examples of monitored AEs included musculoskeletal pain beyond typical soreness, falls, excessive dyspnea, cardiac symptoms, oxygen desaturation >4%, and skin irritation from equipment.

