**Methods/design:**

The study will be a single-blinded pragmatic randomized controlled trial involving patients (*N* = 100) with lung transplants. All patients will receive 6 weeks of treatment, while they will be divided into two groups and receive MIRP (*n* = 50) and conventional rehabilitation treatment (*n* = 50). Clinical functional assessment will be performed before, after intervention, and 3 months after the enrollment, respectively. Adults who have undergone unilateral or bilateral lung transplants and have just returned to the regular ward from the intensive care unit are eligible to participate.

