For this clinical study, we would assess 6 min walk distance (6MWD) as the primary clinical outcome. Previous studies have established an association between 6MWD and survival in patients after solid organ transplantation; shorter 6MWD is associated with increased risk of death, hospitalizations, and worse quality of life in patients evaluated for liver transplantation (18). There have been two key randomized clinical trials (RCTs) evaluating the impact of pulmonary rehabilitation (PR) on standard care after LT (19, 20). However, it remains difficult to conclusively attribute improvements in exercise capacity to the intervention itself. This is primarily due to the significant confounding factor of natural postoperative recovery. Furthermore, the minimal clinically important difference (MCID) for the 6MWT in an LT population has not been established, making it challenging to interpret the true clinical significance of any observed changes. This study aimed to contribute to this evidence base by evaluating a novel multimodal rehabilitation protocol.

Potential limitations of all previous RCTs that examined post-LT interventions include: (1) none used multimodal interventions, (2) the majority of studies were at high risk of bias, (3) lack of follow-up, and (4) some studies did not report critical outcomes such as 6 min walk distance. Thus, high-quality RCTs are needed. While previous studies with single interventions have demonstrated some effectiveness (10, 21), multimodal approaches have not been examined in individuals undergoing lung transplant (LTx). However, multimodal and multidisciplinary aftercare intervention was recommended after kidney transplantation (KTx); the intervention significantly improved outcomes after KTx (22). This study is a randomized controlled trial (RCT) designed to evaluate a novel MIRP against usual care in LTx recipients. Recognizing that conventional post-transplant rehabilitation often lacks the intensity and multidisciplinary focus needed to address multifaceted recovery challenges, MIRP integrates structured, high-frequency components—including chest physiotherapy, progressive strength training, and swallowing therapy—to target these evidence gaps directly. This report describes the research design and protocol for implementing and assessing this RCT.

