### Study hypothesis and objective

This protocol was written in accordance with the Standard Protocol Items: Recommendations for Interventional Trials (SPIRIT) (23). Participants were recruited from the Lung Transplantation Department of the Center of Respiratory Diseases, China-Japan Friendship Hospital, China. The multimodal intensive rehabilitation program is designed to comprehensively improve patients’ respiratory muscle function, voice and swallowing function (24), and limb strength, thereby shortening hospital stay and improving the quality of life. The primary outcome was to analyze the effects of MIRP on the 6 min walking distance in lung transplant recipients. Secondary outcomes were (1) short-term change in health-related quality of life; (2) body skeletal muscle mass and skeletal bone condition; (3) respiratory muscle function and lung function; (4) psycho-emotional states; (5) the state of swallowing function and nutrition; (6) Clinical Frailty Scale; and (7) adverse events related to rehabilitation.

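### The protocol names 6MWD as primary in three sections but an undefined treatment failure as primary in Outcome measurement, and its visible text does not say which visit is primary for 6MWD

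*Protocol article*

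**What the plan says.** Three sections of the protocol article point to 6MWD.

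- Background: "For this clinical study, we would assess 6 min walk distance (6MWD) as the primary clinical outcome".
- Study hypothesis and objective: "The primary outcome was to analyze the effects of MIRP on the 6 min walking distance in lung transplant recipients". The seven secondary outcomes that follow do not include treatment failure.
- Sample size: the calculation uses only 6MWD, with means of 339 m and 320 m and an SD of 20 m, described as "derived from our center’s preliminary pre-study data". It does not say at which time after transplantation those means were measured.

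Outcome measurement says something else: "The primary outcome measure of treatment failure is assessed at 3 months after recruitment". The next sentence opens the list of other measures: "The following are assessed at 6 weeks and 3 months after recruitment, including". That list does not contain 6MWD.

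On timing, the Abstract states: "Clinical functional assessment will be performed before, after intervention, and 3 months after the enrollment, respectively". It does not mention 6MWD or single out a primary visit. Participant timeline refers the schedule to Figure 1, which is not shown here. Its legend includes the 6 min walk test without a time.

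**The concern.** A confirmatory trial needs one primary outcome at one time, or a stated rule for handling several. Here the section that should fix the outcome contradicts the sections that state the objective and justify the sample size. A reader of the final report could not tell from this article whether the planned primary result was 6MWD at 6 weeks, 6MWD at 3 months or some form of failure at 3 months.

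The published protocol is the public reference against which selective reporting is judged, so the ambiguity matters even if the investigators have a single outcome in mind. Two features of the trial sharpen this. According to Blinding, participants, care providers and the research team know the allocation. (That section also says blinding of outcome assessors would be subverted, whereas Outcome measurement says assessors are blinded. That is a separate conflict.) And Trial status gives a planned database lock of December 2025, so the time to settle the matter before looking at results by arm is short.

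**Working it through.** **Step 1. Compare the statements.**

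| Section | Primary outcome | Time |
|---|---|---|
| Background | 6MWD | none given |
| Study hypothesis and objective | 6MWD | none given |
| Sample size | 6MWD means, 339 m v 320 m, SD 20 m | none given |
| Outcome measurement | treatment failure | 3 months |

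Treatment failure occurs once in the document, with no definition, scale, expected rate or effect size. No other visible section reconciles it with 6MWD. The contradiction needs no arithmetic.

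**Step 2. Is the visit for 6MWD fixed elsewhere?** Outcome measurement gives a reason for each visit: 6 weeks for the immediate effect at the end of supervised treatment, 3 months for whether the gains last. Only the 3-month visit is called key. The Abstract gives general times for functional assessment (before, after the intervention, 3 months). None of this ties the primary 6MWD comparison to one visit. The only time attached to a primary outcome is 3 months, and it is attached to treatment failure.

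**Step 3. What the sample size supports.** The plan states 35 per group before dropout. With its own inputs, a two-sided 5% superiority test at 90% power needs

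n = 2 × [20 × (1.96 + 1.28) / (339 − 320)]² = 2 × (64.8 / 19)² = 23.3, so 24 per group.

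The stated 35 is not reproduced this way. That, and the non-inferiority margin of 30 quoted beside it, are separate matters on which this point does not depend. What counts here is that every input is a 6MWD quantity. The stated alpha of 0.05 and power of 90% therefore belong to 6MWD, with the visit left open, and say nothing about treatment failure.

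**Step 4. Illustration of what an open visit could cost.** Suppose 6MWD were tested at both visits, each at two-sided 5%, and the better result reported. Under no effect at either visit, with Z1 and Z2 standard bivariate normal with correlation ρ,

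type I error = 1 − P(|Z1| < 1.96 and |Z2| < 1.96).

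The document gives no between-visit correlation, so ρ is assumed:

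| ρ (assumed) | P(neither rejects) | Type I error |
|---|---|---|
| 0.5 | 0.909 | 9.1% |
| 0.7 | 0.917 | 8.3% |
| 0.8 | 0.922 | 7.8% |
| 0.9 | 0.930 | 7.0% |

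The upper limit under independence is 1 − 0.95² = 9.75%.

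**The case against.** The strongest reply is that the intended reading is easy to recover. Outcome measurement first gives the primary outcome with its time, 3 months, and then lists the other measures, which largely follow the secondary outcomes. On that reading the name of the outcome is a slip, 3 months is the primary time, and the absence of 6MWD from the list is unremarkable. The list also omits the Clinical Frailty Scale, which is a stated secondary outcome, so it is not complete in any case. This is plausible, and it is why the fix below starts from 3 months. But the document does not say it, and if the sentence is left over from another text, its time may be left over too.

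A second reply is that Figure 1, the full protocol, the analysis plan or the registration may settle the visit. For the visit that may be so, and it limits what can be claimed. It does not excuse the naming conflict, which is two incompatible statements in one document and not a detail left to another.

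Three stronger readings are tempting and are not supported.

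- A reader might infer that 6MWD has no assessment time at all. Figure 1 may list the walk-test visits, and the Abstract gives general times. What is missing from the visible text is which visit is primary.
- A reader might infer that the stated alpha and power attach to nothing. Sample size attaches both to 6MWD; only the visit is open.
- A reader might infer that the trial is underpowered for a binary failure outcome. The document gives neither the scale of treatment failure nor any rate, so no power can be stated for it.

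**Conclusion.** The contradiction stands and should be corrected: 6MWD is primary in the objective and the sample size, and an undefined treatment failure is primary in Outcome measurement. That the visit for 6MWD is not fixed stands for the visible text only, because Figure 1 is not shown; a list of several visits there would still not choose the primary one.

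The 7.0% to 9.1% type I error rests on assumed correlations of 0.9 to 0.5 and on a choice of the better visit made after seeing data. It shows what the ambiguity would permit. A reader might take it as the error rate of this trial's analysis, but no passage proposes such a procedure.

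**What to change.** Before any comparison by arm:

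1. Replace the sentence in Outcome measurement with: *The primary outcome is 6MWD at 3 months after recruitment; 6MWD at 6 weeks is secondary.* Three months is the only time the text attaches to a primary outcome. If the 339 m and 320 m in Sample size are 6-week values, name 6 weeks as primary instead, so that the outcome and the calculation agree.
2. Delete treatment failure.
3. Check the result against Figure 1 and the trial registration, and record the date of the correction relative to database lock.

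The cost is a short text correction and a registry check. It should need no new data, provided that 6MWD is collected at the chosen visit; the Abstract's general assessment times suggest so, and the check against Figure 1 would confirm it.
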